### 2.5. Statistical Analysis

Data will be summarized using descriptive statistical methods. Continuous variables will be presented as means and standard deviations, whereas categorical variables will be expressed as frequencies and percentages. Normality of continuous variables will be assessed using the Shapiro–Wilk test.

Baseline demographic, anthropometric, and clinical characteristics will be compared across the three study groups to assess baseline comparability. Continuous variables will be analyzed using one-way analysis of variance (ANOVA) or the Kruskal–Wallis test, as appropriate, whereas categorical variables will be compared using Pearson’s chi-square test or Fisher’s exact test. Ordinal variables will be analyzed using the chi-square test for trend where applicable. If clinically meaningful baseline imbalances are detected, adjusted analyses using mixed-design ANCOVA models will be conducted.

The primary analysis will follow the intention-to-treat principle, whereby all randomized participants will be analyzed in the groups to which they were originally allocated, regardless of adherence to the intervention protocol or study completion. Missing data will be examined before analysis by assessing the extent and pattern of missingness. Where appropriate, missing values will be handled using multiple imputation procedures, and sensitivity analyses will be performed to evaluate the robustness of the findings.

To investigate changes across the 4-week BB intervention period (Time factor) and differences among the three groups (experimental, placebo, and control), a mixed-design analysis of variance (ANOVA) will be performed. The assumptions of the mixed-design repeated-measures ANOVA, including normality of the model residuals, homogeneity of variances, and sphericity, will be assessed before analysis. This analysis will assess the main effects of Time (within-subjects factor) and Group (between-subjects factor), as well as their interaction [78]. When significant effects are identified, post hoc pairwise comparisons will be performed with appropriate adjustment for multiple comparisons. If clinically meaningful baseline imbalances are detected, adjusted analyses using mixed-design ANCOVA models will be conducted.

The clinical relevance of the findings was determined using partial eta squared (η^2^) as an index of effect size. Effect sizes were interpreted as small (η^2^ ≥ 0.01), moderate (η^2^ ≥ 0.06), or large (η^2^ ≥ 0.14) [67]. For continuous outcomes, estimated mean differences, standardized effect sizes, exact *p*-values, and corresponding 95% confidence intervals (95% CI) will be reported as appropriate. For categorical outcomes, odds ratios with 95% CI will be reported where applicable. All statistical analyses will be performed using SPSS version 29.0, with statistical significance set at *p* < 0.05.

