## 2. Materials and Methods

### 2.1. Participants

A total of 54 professional male and female athletes aged 18–25 years will be recruited from collaborating sports clubs located in the Attica region of Greece. Eligible participants will be athletes participating in open-skill sports, including football, basketball, volleyball, and handball, who have sustained at least one chronic lower-limb musculoskeletal injury lasting more than three months. Recruitment will be conducted in collaboration with team coaches and sports medicine professionals affiliated with these clubs. Participants will be randomly assigned in a 1:1:1 ratio to one of three groups: the experimental group, the placebo group, or the control group (*n* = 18 per group). Randomization will be performed using a computer-generated random allocation sequence by an independent researcher who is not involved in participant recruitment, outcome assessment, or statistical analysis. Allocation concealment will be ensured using sequentially numbered, opaque, sealed envelopes. Participants, outcome assessors, and statisticians will remain blinded to group allocation throughout the study.

Sample size was calculated using G*Power software (version 3.1.9.7; Heinrich Heine University Düsseldorf, Düsseldorf, Germany) [47]. The calculation was based on a mixed-design repeated-measures ANOVA with three groups (experimental, placebo, and control) and three measurement time points (baseline, post-intervention, and four-week follow-up). Assuming a medium effect size (f = 0.25), an alpha level of 0.05, statistical power of 0.95 and equal allocation across groups, the minimum required sample size was estimated at 48 participants. To account for an anticipated dropout rate of approximately 10%, the final target sample size was set at 54 participants, with 18 participants allocated to each group. A medium effect size of Cohen’s f = 0.25 was selected as a realistic estimate for a non-invasive psychophysiological intervention (BB) targeting psychological and Performance outcomes. This estimate was considered appropriate because previous intervention studies examining kinesiophobia and rehabilitation-related outcomes in athletes with lower-limb injuries have reported comparable sample sizes (33–51 athletes) and medium effect estimates (0.25–0.40) [48,49,50].

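### Baseline adjustment depends on an undefined imbalance found after the groups are compared; adjusting every continuous outcome for its own baseline by prespecification would be more precise and remove the discretion

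*Protocol article*

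**What the plan says.** All of this is in the protocol article, section 2.5. Statistical Analysis, unless another section is named.

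- Baseline comparison: "Baseline demographic, anthropometric, and clinical characteristics will be compared across the three study groups to assess baseline comparability". The methods listed are one-way ANOVA or Kruskal–Wallis, and chi-square or Fisher tests.
- Adjustment rule: "If clinically meaningful baseline imbalances are detected, adjusted analyses using mixed-design ANCOVA models will be conducted". The sentence appears twice, once after the baseline comparisons and once after the main model.
- Main model: for change over time and differences among the groups, "a mixed-design analysis of variance (ANOVA) will be performed". It tests Group, Time and their interaction. Section 2.1. Participants gives three time points, of which baseline is the first.
- Population: under intention to treat, "all randomized participants will be analyzed in the groups to which they were originally allocated", whatever their adherence or completion.
- Missing data: "Where appropriate, missing values will be handled using multiple imputation procedures", followed by sensitivity analyses.

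**The concern.** In a randomised trial, baseline differences between groups are chance. The value of a baseline covariate lies in how well it predicts the outcome, not in whether the groups happen to differ on it. A rule that adjusts only after an imbalance is seen has two costs.

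- It leaves the analyst to decide, after looking at data, what counts as clinically meaningful, which covariates enter and for which outcomes. The article has many outcomes: TSK-17, four SSR parameters, a set of HRV indices at rest and in three recovery phases, SCAT, PBPI, grip, VO2 measures and lactate.
- In most trials the adjustment will not be made, so the precision it offers is lost. With 18 athletes per group, that matters.

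The default model does use the baseline value, but inefficiently. With baseline as a Time level, the interaction compares groups on within-athlete changes. The Group main effect averages over all three visits, including one at which no treatment has been given.

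**Working it through.** **Inputs.** From section 2.1: three groups of 18, three visits, f = 0.25, alpha 0.05, power 0.95, minimum 48, dropout about 10%, target 54. The correlation r between baseline and later values is not given, so 0.3 to 0.8 is assumed. The only nearby figure is the TSK-17 test–retest ICC of 0.78 in section 2.3.1, which comes from people with chronic low back pain. The TSK entry range of 17 to 37, on a 17 to 68 scale, would tend to lower r here.

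**The plan's own figure.** "Assuming a medium effect size (f = 0.25), an alpha level of 0.05, statistical power of 0.95" leads to "the minimum required sample size was estimated at 48 participants". Using the noncentral F for the interaction, with lambda = f² × N × 3/(1 − r), 4 numerator df, 2(N − 3) denominator df and sphericity:

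- r = 0.5 requires 52, and power at 48 is 0.930;
- r = 0.55 gives exactly 48.

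Without a stated correlation, 48 can be neither confirmed nor called wrong. The inflation 48/0.9 = 53.3, rounded up to 54, reproduces.

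**Precision.** Take equal variances and the same correlation r between any two visits. Variances are in units common to all contrasts between two groups.

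- One post-baseline visit: change from baseline 2(1 − r); baseline-adjusted 1 − r²; ratio (1 + r)/2.
- Mean of both post-baseline visits: change (1 + r)/2 + 1 − 2r; baseline-adjusted (1 + r)/2 − r².

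| r (assumed) | One visit: change | adjusted | ratio | Mean of two: change | adjusted | ratio |
|---|---|---|---|---|---|---|
| 0.3 | 1.40 | 0.91 | 0.65 | 1.05 | 0.56 | 0.53 |
| 0.5 | 1.00 | 0.75 | 0.75 | 0.75 | 0.50 | 0.67 |
| 0.7 | 0.60 | 0.51 | 0.85 | 0.45 | 0.36 | 0.80 |
| 0.8 | 0.40 | 0.36 | 0.90 | 0.30 | 0.26 | 0.87 |

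For one visit, 54 athletes analysed by change give the precision of about 35, 41, 46 and 49 athletes analysed with adjustment (54 × ratio).

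**Group main effect.** If treatment shifts both post-baseline visits by d, the three-visit average shifts by (0 + d + d)/3 = 2d/3. The effect is diluted by a third.

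**What the conditional rule recovers.** A simulation (6,000 runs, 18 per group, a 0.6 SD effect at both post-baseline visits, analysed as their mean) compared three strategies. The trigger was taken as baseline p < 0.05 on the outcome itself, which is an assumption because the article sets no threshold.

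| r | Strategy | Power | Type I error |
|---|---|---|---|
| 0.5 | never adjust | 0.53 | 0.054 |
| 0.5 | adjust if triggered | 0.53 | 0.046 |
| 0.5 | always adjust | 0.69 | 0.047 |
| 0.78 | never adjust | 0.87 | 0.049 |
| 0.78 | adjust if triggered | 0.87 | 0.046 |
| 0.78 | always adjust | 0.91 | 0.052 |

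The trigger fires in about 5% of trials, so the conditional rule performs almost exactly like no adjustment.

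**The case against.** - **The trigger is clinical, not a significance test, and the adjusted analysis may be only supplementary.** Both are fair readings. But significance tests are the only assessment described, and no threshold or covariate is given. If the adjusted analysis is supplementary, the main analysis is never adjusted, and the precision loss is complete.
- **The plan is valid as it stands.** This holds. Simulated type I error was 0.046 to 0.054 for all three strategies. A reader might infer that conditional adjustment produces false positives; nothing here shows that.
- **The correlations are assumed.** They are, and they will differ between questionnaires, SSR, HRV and fitness measures. The size of the gain therefore varies by outcome. Its direction does not, for any positive r below 1 under the equal-variance model above.
- **Dilution touches only the main effect.** Correct: the interaction is not diluted in this way. The article nevertheless tests both and does not say which one answers the treatment question.
- **Missing data are already dealt with.** A reader might infer that the mixed ANOVA is a complete-visit analysis under an intention-to-treat label, losing 5 to 6 athletes (54 × 0.10 = 5.4). The article does not support this. It states no complete-case analysis, and it plans that "missing values will be handled using multiple imputation procedures, and sensitivity analyses will be performed to evaluate the robustness of the findings". With imputation all 54 stay in. What stands is that the qualifier opening that sentence leaves open when imputation is used, while the commitment to analyse everyone is unconditional.

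**Conclusion.** The point holds as one of efficiency and analyst discretion. The article twice makes adjustment depend on an undefined imbalance judged after the data are seen. Prespecified adjustment for the baseline outcome would cut the variance of a group contrast by 35% to 10% at one post-baseline visit, and by 47% to 13% for the mean of both, as r runs from 0.3 to 0.8. At r = 0.5 the cuts are 25% and 33%. These figures assume equal variances and a common correlation across visits; r itself is not in the article.

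A reader might also infer that the ANCOVA would have the baseline outcome as both response and covariate. That would need the imbalanced variable to be the baseline outcome and baseline to remain a Time level within the ANCOVA. The article sets neither condition, so this is not claimed.

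The change should be made, but the planned analysis is not invalid without it.

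**What to change.** In section 2.5:

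1. For every continuous outcome, prespecify a baseline-adjusted model with the post-intervention and follow-up values as responses. SPSS MIXED with group, visit, group-by-visit, baseline outcome and baseline-by-visit is one example. Report the group contrasts at each visit.
2. Delete both copies of the conditional ANCOVA sentence and the baseline significance tests that feed it. Keep a descriptive baseline table.
3. Keep multiple imputation and state it unconditionally. A mixed model on post-baseline values alone would leave out an athlete with none; imputation keeps such athletes within the commitment to all randomised participants.

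The cost is a revised analysis paragraph and different SPSS syntax. Baseline values are already scheduled for these outcomes and SPSS is already the named package, so no new data are needed. Section 2.1 bases the sample size on the mixed ANOVA. One sentence there should say that the calculation was made for that model, and should state the correlation used.

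### Section 2.5 tests Time, Group and Group × Time at 5% without naming which one judges the treatment effect, and the Group test averages in the pre-treatment visit

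*Protocol article*

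**What the plan says.** Section 2.5 of the protocol article describes a single mixed-design ANOVA and states: "This analysis will assess the main effects of Time (within-subjects factor) and Group (between-subjects factor), as well as their interaction". The follow-up rule is: "When significant effects are identified, post hoc pairwise comparisons will be performed with appropriate adjustment for multiple comparisons". The section closes "with statistical significance set at *p* < 0.05", which applies to all analyses. It does not single out one of the three F tests as the test of the treatment hypothesis.

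Section 2.1 bases the sample size on the same model with "three measurement time points (baseline, post-intervention, and four-week follow-up", so baseline is a level of the Time factor.

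Section 2.5 also allows adjusted models (mixed-design ANCOVA), but only when a clinically meaningful baseline imbalance is found. It gives no threshold for that.

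**The concern.** The three F tests answer different questions.

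- **Time** pools the arms and asks whether the athletes as a whole changed. It contains no between-group comparison. All arms listen to music for 20 sessions, so a shared change is plausible.
- **Group** compares the arms on the average of all three visits, including the one before treatment. It is diluted, and it picks up any chance baseline difference that persists.
- **Group × Time** asks whether change over time differs between arms. Of the three, it addresses the treatment question most directly, but it spreads the effect over four degrees of freedom.

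The follow-up rule lets any of them open pairwise testing. With no decisive test fixed in advance, a group claim could rest on whichever of the two group-related F tests reached 5%. A real effect could also be written up as showing no main effect of Group.

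**Working it through.** **1. The plan's own figure.** Section 2.1 gives: "Assuming a medium effect size (f = 0.25), an alpha level of 0.05, statistical power of 0.95 and equal allocation across groups", and from this "the minimum required sample size was estimated at 48 participants". The correlation between visits (ρ) is not stated, so it has to be assumed. With m = 3 visits and no sphericity correction:

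- Interaction: λ = f²·N·m/(1−ρ), df 4 and 2(N−3). At N = 48, ρ = 0.5: λ = 0.0625 × 48 × 3/0.5 = 18, power 0.930. Power of 0.95 needs N = 52, or 54 in multiples of three. N = 48 is reached for ρ of about 0.55–0.57.
- Group: λ = f²·N·m/(1+2ρ), df 2 and N−3. At N = 48, ρ = 0.5: λ = 9/2 = 4.5, power 0.43. Power of 0.95 needs N = 168 (135–219 for ρ = 0.3–0.8).
- Dropout: 48/0.9 = 53.3, rounded up to 54, which matches "To account for an anticipated dropout rate of approximately 10%, the final target sample size was set at 54 participants".

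So 48 is reproduced only with an assumed ρ. It fits a within-subject or interaction test; the stated 0.95 power cannot belong to the Group test.

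**2. Dilution.** If one arm shifts by d at both post-baseline visits, its three-visit mean shifts by (0 + d + d)/3 = 2d/3.

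**3. Null error rate.** Each F test has size 0.05. For Group or interaction, treated as independent: 1 − 0.95² = 0.0975. Simulation with 18 per group and compound symmetry (ρ from 0.3 to 0.78) gives 0.097–0.099; AR(1) with ρ = 0.5 gives 0.102. For any of the three tests: 1 − 0.95³ = 0.143. The Group F alone simulates at 0.050–0.052.

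If a claim also needs a Bonferroni-adjusted pairwise difference (marginal means after Group, a post-baseline visit after the interaction), the simulated rate is 0.049–0.057. Bonferroni within each visit is an assumption, because the article does not name the adjustment.

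**4. Power for a 0.8 SD effect** at both post-baseline visits in one arm, n = 18 per group, compound symmetry:

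- Group: λ = 8nd²/[9(1+2ρ)] = 10.24/(1+2ρ), df 2 and 51.
- Interaction: λ = (4/9)nd²/(1−ρ) = 5.12/(1−ρ), df 4 and 102.
- Baseline-adjusted contrast on the mean of the two post visits: λ = (2/3)nd²/[(1+ρ)/2 − ρ²] = 7.68/[(1+ρ)/2 − ρ²], df 2 and 50.

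| ρ (assumed) | Group | Interaction | Baseline-adjusted |
|---|---|---|---|
| 0.3 | 0.59 | 0.54 | 0.906 |
| 0.5 | 0.49 | 0.71 | 0.936 |
| 0.78 | 0.39 | 0.98 | 0.997 |

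Simulation agrees (baseline-adjusted: 0.90, 0.93, 0.996) and gives the adjusted test a null size of 0.048–0.051. The last column uses both post visits and assumes an equal effect at each. At the post-intervention visit alone, adjusted power is 0.70 at ρ = 0.3 and 0.79 at ρ = 0.5, still above the interaction.

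**5. Sensitivity to baseline differences.** With a fixed 0.4 SD difference in one arm at all three visits, no treatment effect and ρ = 0.5, the Group F rejects in 30% of trials, the interaction in 5% and the baseline-adjusted contrast in 12%. These rates are conditional on that difference. Over all randomisations the Group F stays at 5%.

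**The case against.** A reader might infer that the article makes the three tests co-equal and lets any of them prove efficacy. It does not say so. Assessing both main effects and the interaction is the normal output of this model. A significant effect only opens pairwise comparisons, which are adjusted, and mean differences with confidence intervals are also promised. The 9.75% is therefore not the plan's stated error rate. It applies only if an omnibus F is taken as the claim.

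A reader might also infer that the Group test is invalid as a test of treatment. Under the 1:1:1 randomisation in section 2.1 it has correct 5% size; it is a poor test, not an invalid one. Nor is it always weaker than the interaction: at a correlation of 0.3 it is slightly stronger. A significant Time effect after a real common change is not a false positive either. With a common 0.6 SD trend and no treatment effect, Time is significant in 99.7% of simulated trials, while Group or interaction stays at 0.099.

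Finally, this is a condensed article, and a full protocol or analysis plan may name the decisive test. That would dispose of a complaint about missing detail. It does not dispose of the rule the article does state: any significant effect opens pairwise testing, and baseline adjustment depends on a detected imbalance. The ANCOVA provision is aimed at the baseline problem, but it makes the choice of model depend on the data and, without an imbalance, forgoes the power that adjustment brings.

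**Conclusion.** The point holds in a limited form. The article does not fix which F test carries the treatment comparison, and its follow-up trigger admits one test with no between-group content and one that is diluted by a third and sensitive to baseline differences.

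The chance of a significant group-related F under the null is about 9.75% per outcome if the F itself is the claim, and about 5–6% if an adjusted pairwise difference is also needed. The larger practical loss is power: in the 0.8 SD scenario the baseline-adjusted contrast on the post-visit mean outperforms both group-related F tests throughout the correlations examined, at 5% size. These figures assume 18 per group, compound symmetry, correlation 0.3–0.78 and an equal effect at both post-baseline visits. The documents give none of these correlation or effect-pattern inputs. The point is worth correcting, but it does not show that the planned ANOVA is invalid.

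**What to change.** In section 2.5, state that:

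- the treatment effect for each outcome is judged by the between-group contrast at the post-baseline visits, specified in advance as their mean or a named visit, with the baseline value always a covariate and no longer a level of Time;
- pairwise group comparisons follow from that test only;
- the Group and Time main effects of the mixed ANOVA are descriptive and support no efficacy claim.

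If the sponsor keeps the mixed ANOVA, naming Group × Time as the single decisive test is a weaker but acceptable alternative. Either choice brings the per-outcome rate for the deciding test back to 5%. The baseline-imbalance trigger for ANCOVA then becomes unnecessary for the outcome's own baseline value.

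The cost is a few sentences, with no extra data or participants, provided they are fixed before unblinding. If a full analysis plan already says this, the article should be brought into line with it.

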## Abstract

**Background/Objectives:** This study aims to evaluate the effectiveness of binaural beats (BB) on the autonomic nervous system (ANS), kinesiophobia of reinjury and fitness biomarkers in professional athletes with chronic musculoskeletal injuries. **Methods**: A total of 54 athletes aged 18–25 years, engaged in open-skill sports and experiencing chronic lower-limb injuries for over three months, will be recruited. They will be randomly assigned to one of three groups: an intervention group, a placebo group, and a control group. All athletes will undergo a 15 min auditory intervention five times per week for four weeks. The intervention group will listen to BB embedded in music at high beta and gamma frequencies (30–100 Hz) with guided instructions. The placebo group will receive placebo BB within the same music framework, while the control group will listen only to the music background. Assessments will be conducted at baseline, immediately post-intervention, and at a 4-week follow-up. The primary outcomes will be kinesiophobia of reinjury, ANS function, and heart rate variability (HRV), assessed using the Tampa Scale of Kinesiophobia (TSK-17), Sympathetic Skin Response (SSR), and HRV analysis, respectively. Secondary outcomes will include sport-related anxiety and pain beliefs, assessed using the Sport Competition Anxiety Test (SCAT-15) and the Pain Beliefs and Perceptions Inventory (PBPI-16), respectively; handgrip strength, assessed using the Hand Grip Test; and fitness-related biomarkers, including maximal oxygen uptake (VO_2_max) and blood lactate concentration. **Conclusions**: These findings may provide evidence supporting BB as a complementary, non-invasive intervention to enhance psychological and physiological rehabilitation in injured athletes. Ethics and Dissemination: The study has received ethical approval and is registered on ClinicalTrials.gov. Findings will be disseminated through peer-reviewed publications, conferences, and academic presentations.

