Athletes who participate in open-skill sports were selected because these sports involve unpredictable movement environments, which may increase the risk of lower-limb injury. Therefore, interventions that improve autonomic regulation, such as binaural beats, may help reduce fear of reinjury.

Therefore, based on this theoretical and clinical reasoning, the present study aims to investigate the effects of binaural beat stimulation on kinesiophobia of reinjury, on ANS function through the Sympathetic Skin Response (SSR) and the Isometric Hand Grip test (IHG) and the fitness biomarkers such as VO_2_max, blood lactate concentration, and HRV in professional athletes with chronic lower-limb musculoskeletal injuries (MSK-I). A secondary objective is to examine the maintenance of these effects four weeks after the intervention. It is hypothesized that binaural beats favorably modulate ANS activity, reduce kinesiophobia, reinjury anxiety, and pain beliefs, and enhance aerobic capacity, with sustained effects at follow-up. Conversely, the null hypothesis posits that binaural beat stimulation will not significantly affect ANS function, psychological outcomes, or fitness biomarkers, nor will any effects be maintained after four weeks.

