The BB music-based intervention will be performed prior to each training session or competition, as part of the athletes’ warm-up routine. Athletes will be instructed to conduct the listening sessions in a quiet environment, seated comfortably with their eyes closed, and to avoid distractions from external stimuli during the intervention. All groups will receive the BB music-based interventions for 20 sessions, lasting 15 min per session, 5 times per week, over a period of 4 weeks.

Before beginning the BB music-based intervention phase, all athletes will attend a familiarization session during which the researchers will provide detailed instructions on how to perform the intervention. During the main intervention phase, the first session will be supervised by the research team, while the remaining sessions will be carried out individually, at different times according to each athlete’s training schedule. Each group will randomly receive the BB music-based intervention program.

The intervention group will receive a complete BB music-based intervention program. The placebo group will receive the same music-based intervention program with the verbal guidance but without the binaural beats. The control group will listen only to the music track, with the same music background as the intervention and placebo groups.

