## 5. Strengths and Limitations

A major strength of the present study is its double-blind randomized controlled trial design, which minimizes selection and assessment bias and enhances methodological rigor. The inclusion of experimental, placebo, and control groups allows the specific effects of binaural beats to be examined beyond the potential effects of music exposure and verbal guidance alone. In addition, the simultaneous evaluation of psychological outcomes, ANS function, handgrip strength, cardiovascular regulation (HRV), and fitness biomarkers provides a comprehensive biopsychophysiological assessment of professional athletes in open skill sports with chronic MSK-I. The inclusion of follow-up measurements four weeks after completion of the intervention further enables the examination of short-term maintenance effects.

Another strength of the study is the standardization of the intervention protocol. The binaural beats music-based intervention will be administered through headphones to ensure accurate binaural auditory stimulation. Furthermore, intervention duration, listening frequency, warm-up integration, auditory guidance, and environmental instructions will be standardized across participants to reduce variability in auditory exposure and improve intervention fidelity. The use of validated questionnaires and standardized physiological and functional assessment procedures further strengthens the reliability of the outcome measures and the internal validity of this study.

Nevertheless, several limitations should be acknowledged. First, participants will be recruited from collaborating sports clubs within the Attica region, Greece, which may introduce selection bias and limit the generalizability of the findings to athletes from other geographical regions, competitive levels, or sporting disciplines. Second, the study focuses exclusively on chronic lower-limb MSK-I, restricting the applicability of the findings to acute injuries, upper-limb musculoskeletal conditions, or post-surgical populations.

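### The experimental-versus-placebo comparison, the only one that isolates binaural beats, is left as a gated and adjusted post hoc pair instead of the planned primary contrast

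*Protocol article*

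**What the plan says.** The Introduction states the aim: "the present study aims to investigate the effects of binaural beat stimulation on kinesiophobia of reinjury", together with autonomic and fitness outcomes. The arms are built up in layers:

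- Experimental (Abstract): "The intervention group will listen to BB embedded in music at high beta and gamma frequencies (30–100 Hz) with guided instructions".
- Placebo (section 2.4): "The placebo group will receive the same music-based intervention program with the verbal guidance but without the binaural beats".
- Control (section 2.4): "The control group will listen only to the music track, with the same music background as the intervention and placebo groups".

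Section 5 says that this three-arm design "allows the specific effects of binaural beats to be examined beyond the potential effects of music exposure and verbal guidance alone".

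Section 2.5 plans a mixed-design ANOVA with Time and Group main effects and their interaction. The pairs come afterwards: "When significant effects are identified, post hoc pairwise comparisons will be performed with appropriate adjustment for multiple comparisons". The adjustment method is not named, no pair is singled out, and the effect that must be significant first is not stated. Section 2.1 sizes the trial on the same three-group, three-visit model.

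**The concern.** The design and the analysis are aimed at different targets. Placebo and control differ by guidance, and experimental and control differ by guidance plus beats. Only experimental and placebo differ by the beats alone. A three-group omnibus test responds to any difference among the arms, so a significant result does not show that the beats did anything. The one informative comparison must wait for that test and then share a multiplicity penalty with two pairs that do not isolate the beats.

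Because the gating effect is not named, a Time effect common to all three arms would also satisfy the wording. At stake is the chance of detecting a real beats effect, and clarity about which result would support the trial's claim.

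**Working it through.** **Inputs from section 2.1:** three groups, three visits, f = 0.25, alpha 0.05, power 0.95, 48 participants (16 per arm), raised to 54 (18 per arm) for about 10% dropout.

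**Assumptions, not in the document:** correlation between visits 0.5; outcome SD 1; any effect present equally at both post-baseline visits; sphericity; Bonferroni over three pairs; the interaction as the gate.

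**1. The plan's own figure.** For the Time-by-Group interaction, lambda = N × 3 × f² / (1 − r), with df 4 and 2(N − 3). At N = 48 and r = 0.5, lambda = 48 × 3 × 0.0625 / 0.5 = 18 and power is 0.930. At r = 0.55 it is 0.954. So 48 is reproduced with a correlation slightly above 0.5. Dropout: 48 / 0.9 = 53.3, hence 54.

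**2. What the omnibus test responds to.** If one arm differs from the other two by D at both later visits, interaction f = (2/9) × D. For D = 0.8, f = 0.178 and lambda = 9.10 at N = 48 and 10.24 at N = 54; power is 0.64 and 0.70. For D = 1.125, f = 0.25 and power is 0.93 and 0.96. The formula does not depend on which arm is the odd one out. The power is the same when the beats alone work (experimental differs) and when guidance alone works (control differs).

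**3. False positives on the beats contrast.** Take a guidance-only truth: experimental equals placebo, and both differ from control by 0.8 SD. In simulation, the interaction gate followed by a Bonferroni test of experimental versus placebo rejects in about 1.5% of trials, at 16 or 18 per arm.

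**4. Power for a beats-only effect of 0.8 SD.** The variance of change is 2 × (1 − 0.5) = 1, so SE = sqrt(2/n): 0.354 at n = 16 and 0.333 at n = 18. Noncentrality is 0.8/SE = 2.26 and 2.40, with pooled df 45 and 51.

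| Procedure | n = 16 per arm | n = 18 per arm |
|---|---|---|
| Single planned contrast, alpha 0.05 | 0.60 | 0.65 |
| Bonferroni only, alpha 0.05/3 | 0.42 | 0.48 |
| Interaction gate plus Bonferroni (simulated) | about 0.38 | about 0.44 |

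Most of the loss comes from the shared adjustment (0.60 to 0.42 at n = 16). The gate takes a further 0.04 or so. An easier gate, such as any significant effect, would leave power between the last two rows.

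**5. Range over effect size** (single contrast against gated Bonferroni, n = 16): 0.28 against 0.12 at 0.5 SD; 0.79 against about 0.62 at 1.0 SD. At n = 18: 0.31 against 0.14, and 0.84 against 0.69.

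**The case against.** An omnibus test followed by adjusted pairwise tests is a valid and conservative procedure for three arms. Experimental versus placebo is tested, and the article promises mean differences with confidence intervals. All of that stands.

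A reader might infer that the trial would announce a beats effect from a significant omnibus test when only guidance works. The documents do not support this. Section 2.5 continues to the pairs, section 5 shows that the purpose of the placebo arm is understood, and nowhere is the omnibus result alone said to establish efficacy. The 0.64 to 0.96 in step 2 are power against a real guidance effect, not error rates for a beats claim.

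The size of the loss also depends on assumptions. Bonferroni is not named in the plan. With baseline adjustment at n = 16, the beats-only 0.8 SD case gives about 0.43 (Bonferroni) to 0.46 (Holm) gated, against 0.72 ungated. If beats and guidance each add 0.8 SD, the gate opens in about 99% of trials and gated Holm gives 0.67 against 0.71, so little is lost.

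A separate analysis plan might rank the contrasts. Even so, the article itself fixes the testing order and sizes the trial on the omnibus model.

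A reader might also infer that control athletes, hearing no guidance, can identify their arm despite the claim that "Participants, outcome assessors, and statisticians will remain blinded to group allocation throughout the study". The article does not say what athletes are told about the other tracks, so this is conjecture and a separate matter.

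**Conclusion.** The point holds as a loss of power and a lack of focus on the stated question. It does not show an invalid test or an inflated error rate. The mismatch follows from the arm definitions and the wording of section 2.5 and needs no numerical assumption. Its size does: for a beats-only 0.8 SD effect the plan gives up about 0.60 − 0.38 = 0.22 of power at 16 per arm and 0.65 − 0.44 = 0.21 at 18, under correlation 0.5, change scores, Bonferroni and an interaction gate. The loss is smaller with Holm when guidance also works. Naming the contrast does not by itself make it well powered: 0.60 to 0.65 is still well below the planned 0.95. The improvement is cheap and worth making before any unblinded data are seen.

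**What to change.** In section 2.5, name experimental minus placebo change from baseline, at one stated visit (for example immediately post-intervention), as the primary contrast for each primary outcome. Test it directly at two-sided 0.05, without an omnibus gate and without an adjustment shared with the other pairs. Make experimental versus control and placebo versus control secondary, and label both as including the effect of guidance. State that neither the Time or Group main effects nor the omnibus interaction alone will be taken as evidence that binaural beats work.

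This changes wording only and needs no new data or participants. The cost is that experimental versus control and the omnibus test can no longer carry the headline claim.
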